##### Trial design

Figure 1 gives an overview of the trial design.

**Figure 1 F1:**
[figure not shown]
Flow diagram.

##### **Basic design (including sample size)**

Date of First Randomisation: 18 March 2005

Date of Last Randomisation: 28 November 2008

Target for Randomisation: 600

Number Randomised: 641

**Eligibility criteria**:

1. Written informed consent from the participant

2. Clinical diagnosis of CFS based on Oxford research diagnostic criteria

3. Therapy needs make participation appropriate

4. Aged 18 years or over

5. Adequate level of English comprehension

6. Chalder Fatigue bimodal score of 6 or more

7. SF-36 physical function subscale score of 65 or less

8. No psychiatric exclusions listed in the Oxford research diagnostic criteria

9. Able to attend for therapy and research assessments

10. No contraindications to any of the trial interventions

11. No previous trial therapy at a PACE centre

**Randomised interventions ****(all manuals are available from ****
http://www.pacetrial.org
****):**

1. Adaptive pacing therapy + standardised specialist medical care (APT).

APT is based on the illness model of CFS/ME as a currently undetermined organic disease, with the assumption that APT can improve quality of life while not affecting the core disease other than providing the best conditions for natural recovery. APT is essentially an energy management approach, which involves assessment of the link between activity and subsequent symptoms and disability, using a daily diary, with advice to plan and pace activity to avoid exacerbations.

2. Cognitive behavioural therapy + standardised specialist medical care (CBT).

CBT is based on the illness model of fear avoidance, used in the three previous trials of CBT [39-41]. There are three essential elements: (a) assessment of illness beliefs and coping strategies; (b) structuring of daily rest, sleep, and activity, with a graduated return to normal activity; and (c) collaborative challenging of unhelpful beliefs about symptoms and activity.

3. Graded exercise therapy + standardised specialist medical care (GET).

GET is based on the illness model of deconditioning and exercise intolerance, used in the previous trials [42,43]. Therapy involves an assessment of physical capacity, negotiation of an individually designed home exercise programme with set target heart rates and times, and participant feedback with mutual planning of the next fortnight’s exercise programme.

4. Standardised specialist medical care alone (SSMC).

SSMC is given to all participants and includes visits to the clinic doctor with general, but not specific advice, regarding activity and rest management, such as advice to avoid the extremes of exercise and rest, as well as symptomatic pharmacotherapy. SSMC is standardised in the SSMC Doctor’s Manual. SSMC participants, like all other participants, will already have received the patient clinic leaflet (PCL). There will be no additional therapist involvement, and, in particular, there will be no diary monitoring with consequent advice.

##### **Sample size calculation taken from the protocol (v5.2)**

The following is quoted from the PACE trial protocol (v5.2) (see also [13]) and describes sample size estimation based on percentages responding to the trial interventions. The primary outcomes were changed subsequently to measures on continuous scales.

At one year we assume that 60% will respond with CBT, 50% with GET, 25% with APT, and 10% with SSMC. The existing evidence suggests that at one-year follow-up, 50 to 63% of participants with CFS/ME had a positive outcome, by intention to treat, in the three RCTs of rehabilitative CBT [39-41] with 69% improved after an educational rehabilitation that closely resembled CBT [44]. This compares with 18 to 63% improved in the two RCTs of GET [42,43] and 47% improvement in a clinical audit of GET [45]. For usual medical care 6 to 17% improved by one year in two RCTs [40,41]. There are no previous RCTs of APT to guide us, but we estimate that APT will be at least as effective as the control therapy of relaxation and flexibility used in previous RCTs, with 26 to 27% improved on primary outcomes [39,43].

Our planned intention to treat analyses will compare APT against SSMC alone, and both CBT and GET against APT. Assuming α = 5% and a power of 90%, we require a minimum of 135 participants in the SSMC alone and APT groups, 80 participants in the GET group and 40 in the CBT group [46]. However these last two numbers are insufficient to study predictors, process, or cost-effectiveness. We will have low statistical power to detect the difference between CBT and GET, though our estimates will be useful in planning future trials. As an example, to detect a difference in responder rates of 50 and 60%, with 90% power, would require 520 participants per group; numbers beyond a realistic two-arm trial. Therefore, we will study equal numbers of 135 participants in each of the four arms, which gives us greater than 90% power to study differences in efficacy between APT and both CBT and GET. We will adjust our numbers for dropouts, at the same time as designing the trial and its management to minimise dropouts. Dropout rates were 12 and 33% in the two studies of GET [42,43] and 3, 10, and 40% in the three studies of rehabilitative CBT [39-41]. On the basis of our own previous trials we estimate a dropout rate of 10%. We therefore require approximately 150 participants in each intervention group, or 600 participants in all. Calculation of the sample size required to detect economic differences between intervention groups requires data on cost per change in outcome, which are not currently available.

##### 

**Stratification at randomisation** Allocation of interventions to participants was by minimisation with a random component [47] and four stratification factors:

Centre (6 strata): 1 and 4, 2, 3, 5, 6, 7

CDC Criteria (2 strata): Met or unmet

London Criteria (2 strata): Met or unmet

Current Depressive Disorder (2 strata): Present or absent

Participants found to be incorrectly stratified will be kept in their original strata for the primary analysis in accordance with the principle of intention-to-treat (ITT) [48]. The extent of incorrect stratification will be reported.

#### **
*Data collection*
**

##### 

**Screening measures** A clinic patient log book was kept of all new CFS/ME referrals to trial centres to facilitate monitoring of recruitment to the trial. Screening information will not be used in the analysis except for:

1. Reasons for patients not taking part in the trial (see Participant Flow).

2. Chalder Fatigue Questionnaire and SF-36 Physical Functioning subscale scores where these are not available at baseline (see Method for Handling Dropouts and Missing Data).

##### 

**Baseline and outcome measures** The information collected at baseline and follow-up is presented in Table 2.

**Table 2 T2:** Timing of research assessments

	**Baseline**^ **a** ^	**Week 12**	**Week 24**	**Week 52**	**Discontinuation of therapy**	**Discontinuation of follow**-**up**
**Demographic and clinical data**						
Eligibility	✓					
Centre	✓					
Date of birth	✓					
Gender	✓					
Ethnicity	✓					
Marital status/dependents	✓					
Living arrangements	✓					
Usual place of residence	✓					
Educational level	✓					
Group membership	✓			✓		
Height and weight	✓					
Employment status	✓					
Benefits/pensions status	✓					
Start of current illness	✓					
Start of disabling episode	✓					
Comorbid medical conditions	✓	✓	✓	✓	✓	
Medications and therapies	✓	✓	✓	✓	✓	
Oxford criteria	✓			✓	✓	
CDC criteria/CDC symptoms	✓			✓	✓	
London criteria	✓			✓	✓	
Fibromyalgia	✓			✓	✓	
Past medical history	✓					
Preferred intervention group	✓					
Adverse events		✓	✓	✓	✓	
**Therapist data**^ **c** ^						
Primary qualification	✓					
Years of experience	✓					
Years of relevant experience	✓					
Employment grade	✓					
**Doctor data**^ **c** ^						
Discipline	✓					
Employment grade	✓					
**Questionnaires**						
Chalder fatigue	✓	✓	✓	✓	✓	✓
SF-36 physical functioning	✓	✓	✓	✓	✓	✓
Participant CGI		✓	✓	✓	✓	✓
Doctor CGI				✓	✓	✓
Therapist CGI			✓		✓	✓
Walking test	✓		✓	✓	✓	
Actigraphy	✓					
HADS	✓	✓	✓	✓	✓	
Self-efficacy	✓	✓	✓	✓	✓	
WSAS	✓	✓	✓	✓	✓	
SIQ^b^	✓	✓	✓	✓		
PHQ-15	✓	✓	✓	✓	✓	
Exercise and activity	✓	✓	✓	✓	✓	
Jenkins Sleep Scale	✓	✓	✓	✓	✓	
Step test	✓	✓	✓	✓	✓	
Borg Scale	✓	✓	✓	✓	✓	
Participant satisfaction			✓	✓		
SSMC/therapy adherence			✓	✓	✓	✓
EQ-5D	✓		✓	✓	✓	
CSRI	✓		✓	✓	✓	

^a^Baseline was conducted over two research visits prior to randomisation; ^b^The SIQ is now known as the Cognitive and Behavioural Questionnaire; ^c^The therapist and doctor data will be kept separate from the trial database and summarised by the Trial Manager (see Baseline Comparability of Randomised Groups); Note: CDC, Centers for Disease Control; CGI, clinical global impression; CSRI, client service receipt inventory; EQ-5D, Euroqol 5 dimensions; HADS, hospital anxiety and depression scale; PHQ15, physical health questionnaire 15; SF-36, short-form 36; SIQ, symptoms interpretation questionnaire; SSMC, standardised specialist medical care; WSAS, work and social adjustment scale.

In addition, details were recorded for i) training sessions, ii) therapist competency, iii) quality control checks of therapy sessions, and iv) homework compliance assessments that were made after every therapy session and that will be summarized as part of the general description of intended intervention policies.

Primary and secondary outcome variables will be derived from the follow-up data at each relevant time-point as follows.

Primary outcomes:

i) Fatigue total score (Likert scoring, higher scores indicate more fatigue).

ii) Physical disability total score (sum of 10 items multiplied by 5, lower scores indicate more disability).

Secondary outcomes are presented in Table 3.

**Table 3 T3:** Derivation of secondary outcomes

	**Secondary outcome**	**Derivation**
iii)	Serious deterioration	Absent/present - derived using the DMEC algorithm
iv)	Serious deterioration: Component 1	Absent/present - SF-36 physical function score diminishing by 20 or more points between baseline and any two consecutive assessment interviews
v)	Serious deterioration: Component 2	Absent/present - Participant-rated CGI change score of ‘much worse’ or ‘very much worse’ at two consecutive assessment interviews
vi)	Serious deterioration: Component 3	Absent/present - Withdrawal from therapy more than 8 weeks after randomisation due to participant’s reported worsening of their condition
vii)	Serious deterioration: Component 4	Absent/present - A serious adverse reaction
viii)	Serious adverse events	Total number up to 52 weeks
ix)	Serious adverse reactions	Total number up to 52 weeks
x)	Adverse events	Total number and the proportion of participants having one or more up to 52 weeks
xi)	Withdrawals from intervention	No/yes; person responsible; reason; days from randomisation
xii)	Participant-rated CGI	Positive change; no change; negative change
xiii)	Anxiety (HADS-A)	Total (sum) of the anxiety items of the HADS (higher scores indicate more anxiety)
xiv)	Depression (HADS-D)	Total (sum) of the depression items of the HADS (higher scores indicate more depression)
xv)	Six minute walking test	Total number of meters walked - derived from the number of 10 meter lengths plus any partial distance
xvi)	Work and social adjustment	Total (sum) of all items (higher scores indicate less adjustment)
xvii)	Participant satisfaction	Very satisfied; moderately satisfied; slightly satisfied; neither; slightly dissatisfied; moderately dissatisfied; very dissatisfied
xviii)	CDC Symptoms (#)	Total (sum) of CDC symptoms 1 to 8
xix)	Jenkins Sleep Score	
xx)	CSRI - service costs	Total (sum) costs - derived by assigning costs (£) to each relevant item in the CSRI
xxi)	CSRI - societal costs	Total (sum) costs - derived by assigning costs (£) to each relevant item in the CSRI
xxii)	CSRI - NHS costs	Total (sum) costs - derived by assigning costs (£) to each relevant item in the CSRI
xxiii)	CSRI - insurance/benefit costs	Total (sum) costs - derived by assigning costs (£) to each relevant item in the CSRI
xxiv)	EuroQol	Item scores for Q1 to 5 will be weighted by utility values and summed to produce a total (this can range from −0.59 to 1, with 1 indicating full health)

Note: CDC, Centers for Disease Control; CGI, clinical global impression; CSRI, client service receipt inventory; DMEC, data monitoring and ethics committee; HADS, hospital anxiety and depression scale.

##### 

**Trial periods (recruitment and follow-up)** Recruitment was initially intended to be ongoing for 36 months, with three centres recruiting during the first 12 months, six centres recruiting during the subsequent 24 months, and three centres recruiting at twice the annual rate during the last 12 months. Due to a funding extension, a seventh centre (Bristol) was added and recruitment was ongoing for 45 months.

SSMC is ongoing over 52 weeks; therapy in APT, CBT and GET is ongoing for the first 23 weeks with one booster session between 36 and 52 weeks. Participants are followed up at 12, 24, and 52 weeks.

##### 

**Research visit window definitions** Screening data are collected prior to baseline visit 1; baseline data are collected prior to randomisation. Baseline visit 2 is at least one week after baseline visit 1. Baseline CFQ and SF-36PF should be collected within one month prior to randomisation. Follow-up data should be collected within one week of the expected date where possible. Week 52 follow-up data can be collected at any time after week 52 with no specified upper time limit other than the end of 52 week data collection for the trial (31 January 2010).

When research visits fall outside of the guidance window, they will be analysed according to the most appropriate time point. Specifically, planned visits taking place up to 18 weeks will be used for the 12-week data, while the closest planned visit will be used for the 24- and 52-week data. If a planned visit data is missing, previous unscheduled visit data can be used instead.

Visit windows will be summarised to indicate whether their distribution is similar across interventions; the use of unscheduled visits will also be summarised.

Where variation in visit times is large, or the average visit time differs across interventions, time will be fitted as a continuous instead of a categorical variable. This decision will be made by a consensus judgement of the authors.

#### **
*General considerations*
**

##### 

**Blinding of the statistical analysis** This document has been developed without reference to the PACE trial database. No analyses of outcomes relating to this strategy have been, or will be, conducted prior to final written approval of the analysis strategy by the TSC. Reports have been prepared with data presented descriptively by intervention (coded to maintain blinding) for the closed sessions of the Data Monitoring Committee. Consequently, both DMC and TSC were blind to intervention group, as were the trial statisticians. Data cleaning will be performed as blind to intervention allocation as possible. Decisions made during analysis concerning data or additional analyses will be documented.

##### 

**Trial samples** Numbers (and percentages) of participants satisfying the following definitions will be reported overall and by intervention.

##### 

**Intention-to-treat sample** The intention-to-treat (ITT) sample is defined as all participants who were randomised into the trial included in the intervention to which they were randomised, regardless of the presence or absence of follow-up data. Participants will be included in the stratum in which they were randomised.

##### 

**Available-case sample** The available case sample is defined as all participants who were randomised into the trial, who have any outcome data available for analysis, included in the stratum and intervention to which they were randomised. This sample will be a subset of the ITT sample, excluding randomised participants who have no outcome data.

##### 

**Per-protocol sample** The per-protocol sample is defined as all participants who were randomised into the trial, who met trial eligibility criteria, and who followed their randomised intervention policy at the centre in which they were randomised; they will be included in the intervention to which they were randomised and with their correct stratum. This sample will be a subset of the ITT sample, excluding randomised participants who (i) are confirmed not to have met trial eligibility criteria at randomisation, and (ii) departed from their randomised intervention policy at any point up to 52 weeks.

##### 

**As-treated sample** The as-treated sample is defined for the health economic analyses as all participants who were randomised into the trial and received one of the trial interventions. This sample will be a subset of the ITT sample, excluding participants who have not received any of the four interventions. Participants will be assigned to their received therapy rather than to their randomised intervention if these disagree.

##### 

**Safety sample** The safety sample is the ITT sample for this trial.

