The amount of item-missing data is expected to be minimal. However, if this is not so for any outcome scale then multiple imputation [58,59] at the item-level will be the primary method used. Items will be imputed 100 times [60] separately for each scale (with the exception of the CFQ and SF-36PF, which will be imputed simultaneously). All of the other items for that scale across all time points (including baseline), scores (overall and any subscales) across all time points (including baseline), the four stratification factors at randomisation, randomised intervention, main therapist, and main SSMC doctor will be included in the imputation model.

##### 

**Missing scale data** Missing baseline scale data are not an issue for the primary analysis of efficacy; no missing data are expected for the stratification factors. Where the CFQ or SF-36PF is missing at baseline they will be replaced by the relevant scale at screening. There is specific guidance for missing baseline scale data, and this will be followed [61]. That is, we will use mean imputation of baseline variables assuming baseline and outcome are correlated less than 0.6.

Where the amount of item-missing data is considered minimal, missing outcome scale-data will be handled within the primary analysis by maximum likelihood [57,62] under a similar model for the missing data mechanism assumed for missing item data (see section above). We will report the amount of missing scale data by the percentage of participants who have more than 10% missing item data for each scale reported.

##### **
*Loss to follow-up*
**

Some participants will withdraw from follow-up during the trial, and for these it may be more appropriate to assume data are missing not at random (MNAR). Where more than 10% of randomised participants are lost to follow-up, the impact of this will be investigated in a sensitivity analysis using the weighting approach described by Carpenter, Kenward and White [63] if multiple imputation is the primary method, or comparing selection model and pattern-mixture model therapy effect estimates [64] where maximum likelihood is the primary method.

##### **
*Method for handling multiple comparisons and multiplicity*
**

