##### **Baseline adjustment**

By design factors only

Not applicable

By design factors and additional factors

This is the primary analysis.

##### 

**Model assumption checks** The following assumptions will be checked:

1. Independence of residuals will be checked using the supportive analyses described in Method for Handling Other Clustering Effects section. ICC and within-cluster variance estimates will be reported.

2. Distribution of residuals and random effects will be checked visually using Q-Q plots and histograms of the residuals and by plotting the between-participant variation in participant outcomes and where appropriate the between-centre, the within-doctor but between-interventions, and the between-therapist variation in participant outcomes. Deviations from a Normal distribution would indicate a violation of model assumptions. In this event an alternative approach to the analysis would be investigated.

3. Equal variance of residuals will be checked visually using plots of the standardised residuals against the predicted values.

4. Absence of an intervention-by-centre interaction will be checked in the primary analysis by including fixed contrasts for the intervention-by-centre interaction.

Checks will be made for extreme outliers and points with high leverage. In the event that these are found, the analysis will be reported with and without these observations together with any relevant details.

##### 

**Other analyses supporting the primary analysis** A number of sensitivity analyses will be employed to examine the robustness of the conclusions of the primary analysis to:

1. Categorical responder/improver analysis.

Clinically significant improvement will be taken as a CGI participant score of 1 (very much improved) or 2 (much improved). CGI (P) scores of 3 (a little improved), 4 (no change) and 5 (a little worse) will be considered as non-improvement. CGI (P) scores of 6 (much worse) and 7 (very much worse) will be considered as deterioration. The primary analyses will be repeated replacing the primary outcomes with the CGI (P) (response versus no response versus deterioration) and using mixed-effects logistic regression.

2. Methods for handling missing data.

The primary analysis will be repeated assuming data are missing not at random (MNAR) as described in Method for Handling Dropouts and Missing Data section.

3. Choice of sample.

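### A missing week-52 score may be filled from an earlier unscheduled visit with no lower time bound, and late week-52 scores are capped only by the trial-wide close

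*SAP article*

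**What the plan says.** All references are to the SAP article.

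- **Research visit window definitions.** The guidance is narrow: "Follow-up data should be collected within one week of the expected date where possible". Week 52 is treated differently, with "no specified upper time limit other than the end of 52 week data collection for the trial (31 January 2010". For planned visits outside the guidance window, anything up to week 18 serves as week 12, and "the closest planned visit will be used for the 24- and 52-week data". Then: "If a planned visit data is missing, previous unscheduled visit data can be used instead". The section also promises summaries of visit timing across arms and of the use of unscheduled visits. It allows time to be fitted as continuous if timing varies widely or its average differs by arm, as the authors judge by consensus.
- **Table 2.** CFQ and SF-36PF are collected at baseline and weeks 12, 24 and 52, and also at discontinuation of therapy and at discontinuation of follow-up.
- **Missing scale data.** Where item-missingness is minimal, "missing outcome scale-data will be handled within the primary analysis by maximum likelihood", under MAR.
- **Withdrawals from the trial and losses to follow-up.** A participant with no primary scale data at week 52 is a loss.
- **Loss to follow-up.** "Where more than 10% of randomised participants are lost to follow-up, the impact of this will be investigated in a sensitivity analysis".
- **Other analyses supporting the primary analysis, item 2.** "The primary analysis will be repeated assuming data are missing not at random (MNAR" is listed without the 10% condition, but the item refers back to the missing-data section.
- **Primary analysis (co-primary outcomes).** Primary interest is in the contrasts at 52 weeks.

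**The concern.** The substitution rule has no lower bound, no maximum gap and no rule for choosing among several unscheduled visits, and its wording makes it optional. Therapy runs over the first 23 weeks apart from one later booster session, so a score taken when therapy stopped could be months old and still be analysed as week 52. For that participant, the rule acts as a carried-forward value inside an analysis that is otherwise likelihood-based under MAR. The mixed model has no need of it, because it could use the early score at the time it was taken.

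At the other end, a week-52 score may be taken long after week 52. How long depends on when the participant was randomised.

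Both features affect the time point on which the primary comparisons rest. The listed sensitivity analyses cover the CGI responder outcome, MNAR data and the per-protocol sample. None removes substituted or far out-of-window scores. The rule may also interact with the 10% loss trigger for the MNAR analysis, since the plan does not say whether a substituted score counts as week-52 data.

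**Working it through.** **1. Inputs.** From Basic design: first randomisation 18 March 2005, last 28 November 2008, 641 randomised. From the window section: close on 31 January 2010. From Loss to follow-up: trigger at more than 10% lost. From the sample size section: planned dropout 10%, consistent with its own inflation of 135 / (1 − 0.10) = 150 per group. From the section on clinical importance: MCID of 0.3 SD, translated to 5 SF-36PF points. The plan gives no count of substituted or late visits.

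**2. Effective upper limit for a week-52 score.** Latest week = days from randomisation to the close / 7.

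| Participant | Week 52 reached | Days past week 52 at close | Weeks past week 52 | Latest study week |
|---|---|---|---|---|
| First | 17 March 2006 | 1,416 | 202.3 | 1,780 / 7 = 254.3 |
| Last | 27 November 2009 | 65 | 9.3 | 429 / 7 = 61.3 |

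The guidance window is one week. These are the outer limits the rule permits; the document does not show that any visit was that late.

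**3. Lower limit for a substituted score.** None is stated. The only constraint is that the unscheduled visit precedes the missing planned one.

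**4. Illustrative bias in a contrast (assumed inputs).** Approximate bias = difference between arms in the share substituted × gap between the substituted and the true week-52 score, taking the gap as the same in both arms.

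| Arm difference in share | Gap 0.3 SD | Gap 0.5 SD | Gap 1.0 SD |
|---|---|---|---|
| 2 points | 0.006 SD | 0.010 SD | 0.020 SD |
| 5 points | 0.015 SD | 0.025 SD | 0.050 SD |
| 10 points | 0.030 SD | 0.050 SD | 0.100 SD |

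On the SF-36PF scale: 8% of one arm substituted, none in the comparator, gap 8 points: 0.08 × 8 = 0.64 points. That is 0.64 / 5 = 13% of the MCID, or 0.13 × 0.3 = about 0.04 SD. With equal shares and equal gaps in both arms the bias cancels.

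**5. The MNAR trigger, if substituted scores count as present.** 0.10 × 641 = 64.1, so at least 65 losses are needed (64 / 641 = 9.98%; 65 / 641 = 10.14%). Substitutions that bring the count down to 64: 1 with 65 true losses, 6 with 70, 13 with 77 (12%), 32 with 96 (15%).

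Probability of 65 or more counted losses, binomial with n = 641 and p = true loss × (1 − share filled); the shares are assumed:

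| True loss | None filled | 10% filled | 20% filled | 30% filled |
|---|---|---|---|---|
| 10% | 0.47 | 0.17 | 0.03 | 0.002 |
| 12% | 0.94 | 0.72 | 0.34 | 0.07 |
| 15% | about 1.00 | 0.996 | 0.94 | 0.64 |

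**The case against.** The plan has safeguards. It will summarise visit windows and unscheduled visits, and Description of available data adds the spread of visit timing by arm and the proportion outside guidance. Fitting time as continuous is close to the remedy proposed here. Keeping late observed outcomes is defensible under intention to treat, since discarding them creates missing data. Participants who withdraw from an intervention are still followed up, so stopping therapy does not by itself lead to substitution. Unscheduled visits are not defined, so equating them with the discontinuation assessments in Table 2 is plausible but inferred. The SF-36PF illustration is small, and its 8% share is already 80% of the planned dropout.

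Most of this limits the size of the problem without removing it. The summaries are descriptive. The continuous-time option has no numeric trigger and rests on the authors' judgement, and nothing says that a substituted score would carry its actual date. The argument for keeping late values stands, and the fix respects it.

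Three stronger readings are tempting but not supported:

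- **That week 52 has no upper limit at all.** The trial-wide close is a limit; what is missing is one per participant.
- **That substitution biases therapy arms against SSMC.** The Convention section reserves the word therapy for APT, CBT and GET, so therapy-discontinuation scores may arise mainly there. But scores at discontinuation of follow-up can arise in every arm, and withdrawal from intervention is not confined to the therapy arms. The asymmetry is possible, not established.
- **That the MNAR check is switched off.** This requires substituted scores to count as present, which is not stated, and matters only when true loss is near or above 10%. The list of supporting analyses names the MNAR analysis without repeating the condition, though it refers back to it.

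**Conclusion.** The point holds as a defect in a stated derivation rule. Followed as written, the plan permits an earlier score of any age to occupy the week-52 slot of the primary contrast, and permits a week-52 score as late as about week 254 for the first participant but only week 61 for the last. No planned sensitivity analysis would show the effect of either.

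The actual size and direction of any bias are unknown. The range of 0.006 to 0.10 SD, against the 0.3 SD MCID, rests on assumed differences in substitution (2 to 10 percentage points) and assumed gaps (0.3 to 1.0 SD). The effect on the MNAR trigger is conditional on how substituted scores are counted. At the planned 10% loss, filling a tenth of the losses would lower the chance of triggering from 0.47 to 0.17. The rule should be tightened; the document does not show that the results would be materially wrong.

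**What to change.** 1. Do not place an earlier unscheduled score in the week-52 slot unless it falls in a pre-stated window applied equally in all arms. Otherwise treat week 52 as missing and let the likelihood model use the score at its actual time. The exact bounds are for the trial team to choose and state.
2. Keep late week-52 scores in the main analysis. Report the primary contrasts with and without substituted and far out-of-window scores, with a stated definition of far.
3. Count substituted scores as lost for the 10% trigger, or run the MNAR analysis regardless of it. Make Loss to follow-up and item 2 of the supporting analyses say the same thing.

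The cost is SAP wording, derivation code and one further set of estimates. Slightly more scores would be classed as missing, so precision may fall a little. No new data are needed: collection of 52-week data closed on 31 January 2010, before the plan version dated 2 May 2010.
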